**Figure 1 F1:**
[figure not shown]
A Consolidated Standards of Reporting Trials flow chart of the study.

### Control group

When patients are admitted to the hospital for their first chemotherapy treatment, the researcher will provide exercise guidance for ‘combined aerobic and resistance exercise’ and guide patients through the manual and video for exercise training, informing them of the recommended exercise time, form, method, intensity and precautions. The patients will be followed up monthly to learn their exercise status, and if patients have not persisted in following the recommendations, the researcher will ask patients why in order to help solve their problems and to encourage them to persist in exercise training.

### Intervention group

The family-involvement combined aerobic and resistance protocol to be applied in the intervention group is described in detail in table 2.

**Table 2 T2:** Exercise training intervention with family members

Guidance for family members	Evaluate the patients’ life and social environment through family members and explain to family members the importance of family members accompanying the patient during exercise.	
	Distribute exercise manuals to family members and play exercise instructional videos.	
	Instruct family members to master the exercise time, method, standard posture and precautions, as well as precautions for the use of elastic bands and dumbbells for patients with BC.	
Supervision of family members	Issue supervision diaries to family members*	Instruct and remind family members regarding the completion of the supervision diary through WeChat or phone every month.
		On readmission to the hospital, the patient will be required to bring the supervision diary in order for the record in the diary to be checked.
	Supervision of family members via WeChat	Establish a special WeChat group for family members, send exercise-related health knowledge to the WeChat group every week and regularly remind family members to urge patients to exercise.
		Encourage family members to ask questions actively in the WeChat group and provide timely feedback on the supervision situation and their feelings, answering relevant questions from family members in the process of guiding and supervising patients.
		Provide appropriate praise and rewards to the family members who complete the monitoring goals every week first, forming a competition mechanism to stimulate interest.
Follow-up with family members	Make phone calls or complete face-to-face follow-up with family member monthly, asking them about questions they encountered during the care of the patients and answering those questions.	
	Ask the patient about the training situation. If patients’ exercise completion are poor, further inquire about why and analyse the reasons, helping the family to solve the problem.	
Instructions to family members		
Family members will accompany patients	Participate in the whole process of the patient’s exercise protocol and provide the patient with full emotional support. Before exercising, choose the method of aerobic exercise together with the patient according to the patient’s preference and play music to help the patient relax while they exercise.	
Family members will supervise patients	Give exercise guidance to the patient, informing the patient of the correct exercise method by playing the provided video. When the patient makes an error or non-standard movement during the exercise, provide timely correction.	
	Supervise the patient exercising. Take photos or videos while the patient is moving to record the patient’s movement. Keep a supervision diary after each exercise session and upload exercise photos or videos in) the WeChat group to ensure the effect of family supervision.	
Family members will encourage patients	Encourage and support the patient to enhance their confidence; encourage the patient to describe difficulties encountered during exercise and ensure them that the patient and family member will overcome the difficulty together.	

*The first part of the supervision diary includes basic information, including initials of family members, initials of patients, the relationship between family members and patients, patients’ height and weight, initials of the doctor in charge, date of chemotherapy, and so on. This part is filled out by the researcher before the diary is distributed to the family members. The second part includes the exercise date, time, location, exercise duration, frequency and number of groups, the patient’s exercise status and whether the family member participated in the exercise guidance and supervision throughout the exercise.

BC, breast cancer.

### Combined aerobic and resistance exercise

The designed exercise training intervention will last for 8 weeks, and each patient can select the most comfortable period of the week according to his or her own situation every week. Each training time is scheduled for half an hour after a meal, and participants are instructed to avoid training with an empty or full stomach. Each workout includes aerobic and resistance exercises that are both progressive. A rest period of 5 min is allowed between aerobic and resistance exercise. Aerobic exercise is accomplished by cycling, walking on a treadmill or brisk walking on the ground, depending on the patient’s preference, according to the following schedule: twice per week for 15–20 min in weeks 1–4 and three times per week for 25–35 min in weeks 5–8. For resistance exercise, the patients will use 0.45 kg dumbbells or a mineral water bottle filled with 500 mL of water and a 18 cm brown elastic band with the brand name TheraBand. These items will be provided by the researchers as the main exercise tools for four resistance exercise movements: hip abduction, seated knee raising, raise before standing and standing lateral raise. These exercises are to be completed twice per week in weeks 1–4, with two sets of each exercise and each set consisting of 8–12 repetitions and then three times per week in weeks 5–8, with three sets of each exercise (each set includes 8–12 repetitions), with plenty of rest between sets.^27–30^

#### Hip abduction

This exercise is done in a standing position, with the elastic band around the ankle of one foot while the other foot is on the elastic band. The opposite hand holds the seat, and the supporting foot is firmly planted on the ground to keep the trunk stable. Initially, the buttocks exert force as the elastic band is stretched outward to the side by raising the leg until the angle between the practice leg and the supporting foot is about 30°. After a pause for about 1 s, the leg is slowly lowered to the ground. The exercise is done by alternating the left and right feet between sets.

#### Seated knee raising

This exercise is done in a sitting position with a straight back while holding the seat with both hands, keeping the upper torso upright, stepping on one end of the elastic band with one foot and pulling the elastic band around the ankle of the other foot. The knee is then lifted to the maximum angle of joint activity and the after a pause for about 1 s, slowly lowered. The exercise is done by alternating the left and right legs between sets.

#### Raise before standing

While standing with feet parallel, head straight and looking straight ahead, the dumbbells are held at both sides of the body by both hands. Both arms are then raised in front of the body, and after a pause for about 1 s, the arms are slowly lowered. Participants are instructed to inhale during the horizontal lift and exhale while returning the arms to their original positions.

#### Standing lateral raise

While standing with feet parallel, head straight and looking straight ahead, the dumbbells are held at both sides of the body by both hands. The arms are raised from the sides, with elbows slightly bent and focus placed on the shoulders. Once the arm is raised to a horizontal position, participants pause for about 1 s before slowly lowering the arms to the initial positions. Participants are instructed to inhale during the horizontal lift and exhale while returning the arms to their original positions.

The intensity of aerobic exercise should be moderate; that is, the Borg subjective fatigue scale score should reach 13–14 points (feeling a little hard). The intensity of resistance exercise should be tolerable to the patient. If obvious fatigue and muscle pain occur during or after training, the intensity of physical activity should be appropriately reduced. If patients have severe pain, discomfort and other symptoms, they should immediately stop the activity and be admitted to the hospital for re-examination.^31 32^

During the exercise, family members are instructed to pay attention to the patient’s reactions and to adjust the elastic band or exercise speed and intensity as needed. They must also ensure the patient is not straining or using too much force during exercise to prevent stretching the wound or the place where the catheter is placed. They should also pay attention to the patient’s movement at all times. If the patient experiences dizziness, discomfort or other adverse events, they should be promptly instructed to stop exercising and visit the hospital if necessary.

### Outcome measurements

The outcome measurements for this pilot study will be derived from baseline assessments and clinical outcomes.

### Demographic and clinical characteristics of the participants

A self-designed demographic and clinical data form will be employed to collect the participants’ sociodemographic data (eg, age, educational background, employment status, marital status and household income), the participants’ medical history (eg, date of BC diagnosis, current stage of BC and date and type of treatment) and family members’ sociodemographic data at baseline (T0).

### Primary outcome: CRF

#### Piper Fatigue Scale-Revised (R-PFS)^33^

The R-PFS will be applied to assess the participants’ subjective fatigue. This self-administered questionnaire contains 22 items with scores ranging from 0 to 10 and includes four domains of subjective fatigue. The R-PFS is available in a simplified Chinese version,^34^ with high reliability and validity, and has high reliability in the population with BC.

### Secondary outcomes: muscle power, exercise completion, family intimacy and adaptability and quality of life

Muscle strength, exercise completion, family intimacy and adaptability and patient quality of life will be assessed as secondary outcomes at T0, T1 and T2 using the stand-up and sit-down chair test, grip test, exercise completion rate, FACESⅡ-CV and FACT-B.

#### Stand-up and sit-down chair test (number of times standing up from the chair within 30 s)^35^

This test will be used to evaluate the leg strength of the participant. The test procedure is as follows: (1) an upright chair (or a folding chair) is placed against a wall (for the sake of safety); (2) the participant sit in the middle of the chair with the right and left feet shoulder-width apart, and one foot may be put slightly forward and the other slightly back, while both arms are crossed at the waist and held near the chest; (3) during the test, participants should completely stand up and then completely sit down; (4) the number of times that the participant stands up from and sits down in the chair within 30 s is recorded; and (5) for safety purposes or when necessary, the participant may use his or her arms for assistance.

#### Grip test^32^

This test will be used to evaluate the arm strength of the participants. A CAMRY (model EH101) electronic grip strength metre is used in units of kg/lb. The maximum force is 90 kg/198 lb, and the division value is 0.1 kg/0.2 lb. Participants are in a standing position, with their hands hanging down naturally, while their feet are positioned under the shoulders and hands are held away from the body.

#### Exercise completion rate

This test will be used to assess the performance of the two types of exercise. The exercise completion rate in this study will be calculated by dividing the number of participants in the intervention group who completed 18 or more training sessions (more than 90% of the total training volume) by the total number of people in the intervention group and multiplying that value by 100%.

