According to previous relevant studies,^25 26^ exercise training begins to play a role in improving CRF during the 8-week exercise intervention process. Therefore, the patients will be tested with the stand-up and sit-down chair test and the grip test at the time of the fourth (T1) and eighth (T2) weekends of the intervention. The exercise completion rates in the two groups will be evaluated at these time points, and the researcher will again issue the general information questionnaires, R-PFS, FACESⅡ-CV and FACT-B to evaluate the effects of the exercise intervention. In the process of distributing the questionnaires, if patients are unable to understand the questionnaire items, the researcher will explain the items. A Consolidated Standards of Reporting Trials flowchart for the study is presented in figure 1. The schedule for trial enrolment, intervention and assessment is presented in table 1.

**Table 1 T1:** Schedule of trial enrolment, intervention and assessment

Study period			
	Beginning of intervention (week 0)	Intervention period (week 4)	End of intervention (week 8)
Inclusion/exclusion criteria	×		
Informed consent	×		
Demographic characteristics	×		
Randomisation and allocation	×		
R-PFS	×	×	×
Stand-up and sit-down chair test	×	×	×
Grip test	×	×	×
Exercise completion rate		×	×
FACESII-CV	×	×	×
FACT-B	×	×	×

FACESⅡ-CV, Family Adaptability and Cohesion Scale, Second Edition-Chinese Version; FACT-B, Functional Assessment of Cancer Therapy-Breast; R-PFS, Piper Fatigue Scale-Revised.

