### Data analysis

Statistical analysis of the results will be completed using SPSS software V.25.0. Analysis of covariance will be applied for comparisons between groups, and paired t-tests will be used for comparisons from before to after exercise within a group. Values of p<0.05 will represent that a significant difference has been detected between test results.

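### The exercise completion rate is defined for the intervention group only, and its fixed 18-session cut-off cannot be reached at week 4, although both groups are to be evaluated at weeks 4 and 8

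*Protocol article*

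**What the plan says.** The *Exercise completion rate* section gives an explicit formula. The numerator is the number of "participants in the intervention group who completed 18 or more training sessions (more than 90% of the total training volume"; it is divided "by the total number of people in the intervention group and multiplying that value by 100".

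*Study design* states how the outcome is to be used: "The exercise completion rates in the two groups will be evaluated at these time points". Those time points are "at the time of the fourth (T1) and eighth (T2) weekends of the intervention". Table 1 agrees, marking the outcome at weeks 4 and 8 and leaving week 0 blank. The opening sentence on secondary outcomes also names baseline, saying of all of them together, exercise completion included, that they "will be assessed as secondary outcomes at T0, T1 and T2".

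The section *Combined aerobic and resistance exercise* sets aerobic exercise at "twice per week for 15–20 min in weeks 1–4 and three times per week for 25–35 min in weeks 5–8". Resistance exercise follows the same weekly frequency, and each workout contains both types. The *Control group* section says that control patients are guided in the same type of exercise.

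**The concern.** The definition and the design disagree in two ways. First, the formula mentions the intervention group in both numerator and denominator, while the design calls for a rate in each group. Second, one fixed session count is used at two time points, although the number of sessions scheduled by the earlier one is well below that count.

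Exercise completion is a named secondary outcome. It is also the most direct measure of the rationale in the *Introduction*, where family support is expected to help patients keep exercising. If the rule stays as it is, someone must later decide how controls are classified and what counts as completion at week 4. The *Discussion* says that participants and investigators cannot be blinded, so those decisions could be taken with the data by group in view.

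**Working it through.** **Inputs**
- Schedule (*Combined aerobic and resistance exercise*): 2 sessions per week in weeks 1–4, 3 per week in weeks 5–8. One workout, with its aerobic and resistance parts, is one session.
- Cut-off (*Exercise completion rate*): 18 or more sessions, glossed as more than 90%.
- Assessment times (*Study design*, Table 1): ends of weeks 4 and 8.

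**Step 1: reproduce the plan's figure**
- Sessions by T1: 4 × 2 = 8.
- Sessions in weeks 5–8: 4 × 3 = 12.
- Total by T2: 8 + 12 = 20.
- 18/20 = 90.0%. The number 18 therefore reproduces as at least 90%. Strictly more than 90% would need 19 sessions (19/20 = 95%).

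**Step 2: apply the cut-off at T1**
- The maximum on schedule is 8 sessions, and 8/18 = 44% of the cut-off.
- Reaching 18 by week 4 would take 18/4 = 4.5 sessions per week against 2 scheduled.
- Counting the aerobic and resistance parts separately does not help. The maximum by T1 is then 2 × 8 = 16, still below 18, and 18 would be only 18/40 = 45% of the full programme.
- On schedule, 8 + 3 × 3 = 17 sessions are reached by the end of week 7, so the 18th falls in week 8.
- The T1 rate is therefore 0% for any group whose members follow the schedule.

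**Step 3: what a 90% rule would mean at T1**
- 0.9 × 8 = 7.2, and 7/8 = 87.5%, so only a patient with all 8 sessions would meet it. A responder rule is a blunt measure at T1; a per-patient fraction is not.

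**Step 4: apply the formula to the control group**
- Numerator and denominator both refer to the intervention group, so no control value exists at T1 or T2.
- If the denominator is read as each group's own total and the numerator as that group's completers, T2 gives one proportion per group. These can be compared, because the control group is guided in the same type of exercise.

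**Step 5: baseline**
- No sessions are scheduled before T0, so the fraction would be 0/0. Table 1 already leaves this cell empty; only the collective sentence on secondary outcomes needs to change.

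**The case against.** The best defence is that the intention is clear. *Study design* plainly wants a rate in each group, controls are guided in the same exercise, and a sensible analyst would apply the rule to both groups at T2. The reference to total training volume also suggests that 18 was meant for the whole programme, so one could say that the T1 criterion is simply undefined rather than 0%. This stands in part: the T2 defect lies in the definition and is easily repaired. It does not remove the problem, because the article gives an explicit formula that contradicts its own design, and T1 is left with either an impossible criterion or none.

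A reader might infer more than the documents support:
- **That no valid comparison between groups can be made at all.** This is true only of the formula as written. Once it covers both groups, T2 works.
- **That the analysis method is wrong.** The *Data analysis* section says "Analysis of covariance will be applied for comparisons between groups", which does not suit a yes/no outcome. That is a one-line general statement in a condensed article, and the test for a binary secondary outcome can properly be left to an analysis plan that is not shown.
- **That the cut-off misclassifies patients because sessions grow longer.** By resistance sets (8 × 8 + 12 × 12 = 208), missing two late sessions leaves 184/208 = 88.5%, and missing two early ones leaves 192/208 = 92.3%. The operative rule, however, counts sessions, so the word volume is loose rather than harmful.
- **That exactly 90% versus more than 90% changes results.** The count of 18 governs, so this is a wording slip.
- **That completion is assessed at baseline.** Table 1 shows otherwise.

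**Conclusion.** The point holds in two parts. As written, the completion rate has no control-group value, and at T1 it is 0% for anyone following the schedule, since 8 sessions are scheduled against a cut-off of 18. One of the two planned assessments therefore carries no information. The other needs the formula extended to controls before the groups can be compared.

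This assumes that one workout is one session (counting the two parts separately leads to the same T1 result) and that patients do not exercise well beyond the schedule.

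The point should be fixed but is not critical. Completion is one of several secondary outcomes. It enters neither the primary fatigue outcome nor the sample size, and the article states no mediation analysis that depends on it.

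**What to change.** 1. Define completion per patient, in both groups, as sessions completed divided by sessions scheduled to date: 8 at T1, 20 at T2.
2. Apply the responder rule at T2 only, worded as at least 90% (18 or more of 20 sessions), with each group's own total as denominator. Compare the two proportions with a test suited to a binary outcome, for example Fisher's exact test.
3. Replace training volume with training sessions in the definition.
4. Bring the sentence on the timing of secondary outcomes into line with Table 1, so that exercise completion is not listed at T0.
5. State how control patients' sessions are counted.

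Items 1 to 4 are rewording and need no new visits. Item 5 carries a small cost. The article describes session diaries only for intervention families, while the exercise status of controls is learned at monthly follow-up. Sessions must be counted in the same way in both groups, for example at that existing follow-up; otherwise a difference in recording could pass for a difference in completion.

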#### FACESⅡ-CV^36^

The FACESⅡ-CV will be adopted to assess the participants’ family intimacy and adaptability. A higher score indicates higher intimacy and adaptability. The FACESⅡ-CV is available in a simplified Chinese version, with high reliability and validity.

#### FACT-B^37^

The FACT-B will be adopted to assess the patients’ quality of life. A higher score reflects better quality of life. The FACT-B is available in a simplified Chinese version, with adequate psychometric properties reported among patients with BC.

### Data analysis

Statistical analysis of the results will be completed using SPSS software V.25.0. Analysis of covariance will be applied for comparisons between groups, and paired t-tests will be used for comparisons from before to after exercise within a group. Values of p<0.05 will represent that a significant difference has been detected between test results.

### Data management

After data collection is complete, all handwritten data will be converted to electronic data. All data will be independently recorded by two researchers in Excel spreadsheets. The software will automatically check for inconsistent or problematic data based on the inspection results and generate a data problem table. After all data have been confirmed, reconciled and stored in an electronic database, participants’ identifying information (eg, real name) will not appear in the relevant reports of the trial to protect their privacy. Only researchers directly involved in the analysis of this study will have access to the final trial dataset, which will contain only coded data.

### Data sharing statement

A technical appendix, statistical codes and dataset will be available at any time on request to the corresponding author.

### Patient and public involvement

Patients or the public were not involved in the design of this study and will not be involved in conducting the research or reporting the results.

